### 3.6. Phase 2 Outcomes

First, the feasibility and safety of the exercise programs will be assessed in terms of adverse events, falls and intercurrent problems. In addition, the adherence of each patient to the selected training option will be determined by analyzing the number of sessions completed, the total minutes of training and the percentage of patients that reached the amount of physical activity indicated by the guidelines.

Quantitative outcomes will be collected before the beginning of the training program, at the end of the training program (three months) and at the six-month follow-up.

The primary outcome will be exercise capacity, assessed through the 6-min walking test. Subjects will be instructed to walk with their habitual walking device as far as possible in 6 min. The test will be performed on a 22-m walkway. The patients will have the possibility of slow down and rest if necessary. The total distance walked, the pain-free walking distance and the perceived exertion at the end of the test (Borg Scale 1–10) will be recorded [34] (Table 1).

Secondary outcomes will include the following:Gait speed, assessed through the 10-m walking test.Lower limb strength, evaluated with the 5-time sit-to-stand test.Health-related QoL, measured by the Italian version of the Short Form Health Survey (SF-36).Fear of falling, assessed through the Short Falls Efficacy Scale.Estimated functional capacity, measured by the Duke Activity Status Index.Depression, evaluated by the Beck Depression Inventory—II and the demoralization scale.Heart rate, oxygen saturation and blood pressureLaboratory outcomes: Serum creatinine levels, estimated glomerular filtration rate, Kt/v, glycaemia, total cholesterol and a full blood count will also be determined.Long-term outcomes: Other clinical outcomes, such as mortality and all-cause hospitalization, will be recorded at 3, 6, 12 and 24 months from the end of the exercise program.

A detailed description of secondary outcomes is available in the Supplementary Material 1.

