### 3.10. Statistical Analysis

In the first qualitative phase, descriptive statistics, chi-squared tests and mixed models of analysis will be employed. Regression analyses will be conducted to determine if different variables (e.g., distance from dialysis center and presence of a caregiver) might interfere with patients’ decisions. Furthermore, the physical activity level and physiological and psychological variables assessed at baseline will be considered independent variables in the regression models.

In the second phase, standard methods of analysis for clinical trials will be used. First, baseline comparisons of patient characteristics for each group will be compared for demographics and primary and secondary outcome measures. The data distribution will also be verified through a Shapiro–Wilk test. A two-way repeated measure analysis of variance will be used to compare differences in the primary and secondary outcomes. Within-group comparisons will be performed via paired Student’s t-tests or Wilcoxon tests, as appropriate. If a significantly different distribution between the baseline characteristics of the group is identified, a secondary analysis that employs multivariate modeling to adjust for these factors will be performed (e.g., linear mixed models for repeated-measures analyses with unbalanced design). Moreover, Kaplan–Meier analysis and Cox regression will be used to model incidence rates for long-term clinical outcomes (hospitalization rate and death). Finally, a post hoc power analysis will also be carried out to determine the clinical impact of the findings.

All analyses will be conducted using intention-to-treat. Missing values, though we will make any effort possible to reduce their incidence, will be treated using the multiple imputation procedure. Moreover, a per-protocol analysis to assess the stability of the study’s conclusions will also be performed. Properly gender-oriented analyses will be carried out for most of the outcomes. A *p* value of 0.05 will be considered statistically significant.

Statistical analysis will be performed with SPSS 21.0 (IBM, Armonk, NY, USA) and MedCalc statistical software (version 19.4.0 and following, MedCalc Software bvba, Ostend, Belgium).

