**Outcomes**					
*Phase 1*					
% Patients responders/eligible		X			
Physical and emotional status		X			
Exercise program choices		X			
Factors related to choices		X			
*Phase 2*					
Safety (adverse events, interruptions)			X		
Adherence (% sessions completed)			X		
6MWT (primary outcome)		X	X	X	
Gait speed, lower limbs strength, quality of life, depression, estimated capacity, fear of falling (secondary)		X	X	X	
Biochemical/laboratory markers		X	X	X	
Hospitalizations and mortality				X	X

Abbreviations: U-PA-I: unstructured physical activity increase; S-HB-LI: structured home-based low-intensity; S-SU-LI: structured supervised low-intensity; PPA: physical performance assessment; 6MWT: 6-min walk test.

**Table 2 mps-03-00083-t002:** The different interventions proposed to the patients by the exercise facilitator.

Program	U-PA-I			S-HB-LI			S-SU-LI			PPA Performance Assessment
	Unstructured Physical Activity Increase			Structured Home-Based Low Intensity			Structured Supervised Low Intensity			
*Setting*	Home			Home			Dialysis Center			-
*Frequency*	Daily			Daily			2- or 3-Time a Week			
*Baseline 6MWD (m)*	<200	201–400	>400	<200	201–400	>400	< 200	201–400	>400	-
*Program features*	Walking (mins) Intensity: moderate [27,28]			Walking: rest (min) × reps Speed (steps/min)			Walking * + strength leg extension/leg curl/shoulder abduction (reps × series − load)			
*Week 1*	5	10	15	1:1 × 6 − 60	1:1 × 8 − 60	1:1 × 8 − 72	3 × 2 – 0.5 kg	3 × 3 − 1 kg	3 × 3 – 1.5 kg	-
*2*	5	10	15	1:1 × 6 − 63	1:1 × 8 − 63	1:1 × 8 − 76	3 × 2 – 0.5 kg	3 × 3 − 1 kg	3 × 3 – 1.5 kg	
*3*	10	15	20	1:1 × 8 − 63	1:1 × 8 − 66	1:1 × 8 − 80	4 × 2 − 1 kg	4 × 3 − 1 kg	4 × 3 – 1.5 kg	
*4*	10	15	20	1:1 × 8 − 66	1:1 × 8 − 69	1:1 × 8 − 84	4 × 2 − 1 kg	4 × 3 − 1 kg	4 × 3 – 1.5 kg	
*5*	15	15	20	1:1 × 8 − 66	1:1 × 8 − 72	1:1 × 8 − 88	3 × 3 − 1 kg	4 × 3 – 1.5 kg	4 × 3 − 2 kg	
*6*	15	20	20	1:1 × 8 − 69	1:1 × 8 − 72	1:1 × 8 − 92	3 × 3 − 1 kg	4 × 3 – 1.5 kg	4 × 3 − 2 kg	
*7*	15	20	25	1:1 × 8 − 69	1:1 × 8 − 76	2:1 × 4 − 72	4 × 3 − 1 kg	4 × 4 – 1.5 kg	4 × 4 − 2 kg	
*8*	20	20	25	1:1 × 8 − 72	1:1 × 8 − 76	2:1 × 4 − 76	4 × 3 − 1 kg	4 × 4 – 1.5 kg	4 × 4 − 2 kg	
*9*	20	20	25	1:1 × 8 − 72	1:1 × 8 − 80	2:1 × 4 − 80	4 × 3 – 1.5 kg	4 × 4 − 2 kg	4 × 4 – 2.5 kg	
*10*	20	25	25	1:1 × 8 − 76	1:1 × 8 − 80	2:1 × 4 − 84	4 × 3 – 1.5 kg	4 × 4 − 2 kg	4 × 4 – 2.5 kg	
*11*	20	25	30	1:1 × 8 − 76	1:1 × 8 − 84	2:1 × 4 − 88	4 × 4 – 1.5 kg	5 × 4 − 2 kg	5 × 4 − 3 kg	

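### Kaplan–Meier and Cox are assigned to a hospitalization rate that, in their ordinary form, they do not estimate; if deaths are censored, Kaplan–Meier also overstates the probability of admission

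*Protocol article*

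**What the plan says.** For the long-term outcomes, section 3.10 fixes the method and names the target: "Kaplan–Meier analysis and Cox regression will be used to model incidence rates for long-term clinical outcomes (hospitalization rate and death". It names no competing-event, composite or recurrent-event method.

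Section 3.6 describes the data behind this analysis: outcomes "such as mortality and all-cause hospitalization, will be recorded at 3, 6, 12 and 24 months from the end of the exercise program". Table 1 has a row for "Hospitalizations and mortality" marked only at the 6-month follow-up and in a last column headed 12 months. It has no 24-month column.

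On missing data, section 3.10 says: "Missing values, though we will make any effort possible to reduce their incidence, will be treated using the multiple imputation procedure". The sentence before it reads "All analyses will be conducted using intention-to-treat". The functional measures these rules cover include the primary one: "The primary outcome will be exercise capacity, assessed through the 6-min walking test", tested at baseline, 3 months and 6 months.

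**The concern.** Three questions are folded into one sentence: how many patients are ever admitted, how often patients are admitted, and how many die. The named methods suit the third and only part of the first.

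- **Rate.** All-cause admissions can recur over one to two years. A first-event analysis stops at the first admission, so a programme that prevented second and third admissions would get no credit for it. Section 5 lists fewer hospitalizations among the hoped-for results, so the choice of quantity matters.
- **Death as a competing event.** A patient who dies without having been admitted can no longer be admitted. Censoring that patient treats the admission as still to come, and 1 minus Kaplan–Meier then exceeds the proportion actually hospitalized.
- **Comparison between arms.** Patients choose their own arm. Section 4.2 expects fitness to influence the choice, and section 1 links low activity and poor performance to mortality. Death rates may therefore differ between arms, and the overstatement with them.

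**Working it through.** **Inputs.** The article states no death, admission or dropout rate, so there is no figure of its own to reproduce here. All hazards below are assumptions, taken as constant over time: first admission λh = 0.3 to 1.0 per patient-year, and death without a prior admission λd = 0.02 to 0.20 per patient-year. Horizons are 6, 12 and 24 months (t = 0.5, 1, 2 years).

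**Step 1: probability of first hospitalization.**
- With deaths censored: 1 − KM = 1 − exp(−λh·t).
- With death as a competing event: CIF = λh/(λh + λd) × [1 − exp(−(λh + λd)·t)].

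Example with λh = 0.6 and λd = 0.15:
- 12 months: 1 − exp(−0.6) = 45.1%, against 0.8 × [1 − exp(−0.75)] = 42.2%.
- 24 months: 1 − exp(−1.2) = 69.9%, against 0.8 × [1 − exp(−1.5)] = 62.1%. A simulation of this case gave 62.2%.

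Each cell shows 1 − KM / CIF in %, with the excess in points (computed before rounding):

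| λh, λd | 6 months | 12 months | 24 months |
|---|---|---|---|
| 0.3, 0.02 | 13.9 / 13.9 (0.1) | 25.9 / 25.7 (0.2) | 45.1 / 44.3 (0.8) |
| 0.6, 0.05 | 25.9 / 25.6 (0.3) | 45.1 / 44.1 (1.0) | 69.9 / 67.2 (2.7) |
| 0.6, 0.15 | 25.9 / 25.0 (0.9) | 45.1 / 42.2 (2.9) | 69.9 / 62.1 (7.7) |
| 0.6, 0.20 | 25.9 / 24.7 (1.2) | 45.1 / 41.3 (3.8) | 69.9 / 59.9 (10.0) |
| 1.0, 0.20 | 39.3 / 37.6 (1.7) | 63.2 / 58.2 (5.0) | 86.5 / 75.8 (10.7) |

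The first and last rows bound the assumed range.

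**Step 2: two arms with different death rates.** Take the second and fourth rows as two arms. Kaplan–Meier shows 69.9% in both at 24 months. The proportions actually hospitalized are 67.2% and 59.9%, a difference of 7.3 points that the curves hide.

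**Step 3: what a first-event analysis leaves out.** Let m be the mean number of admissions per patient over follow-up. Ignoring death, first events make up (1 − exp(−m))/m of all admissions if counts are Poisson, and (1 − 1/(1 + m))/m if patients differ by a gamma frailty with variance 1. Assume 0.5 to 1.5 admissions per patient-year over 1 to 2 years, so m = 0.5 to 3.
- Poisson: 79% at m = 0.5, falling to 32% at m = 3.
- Gamma frailty: 67%, falling to 25%.

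**Step 4: the horizon.** Table 1 places the end of training at 3 months, so it counts from baseline and closes at month 12. Section 3.6 counts from the end of the programme, so its last time point is month 24 + 3 = 27 on the Table 1 clock. If the analysis clock starts at baseline (t = 2.25), the excess runs from 1.0 to 11.7 points; at the Table 1 close-out it is 0.2 to 5.0.

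**Step 5: scale of the imputation question.** Here the relevant rate is total mortality, assumed at 0.05 to 0.20 per patient-year, applied to the 88 patients in section 3.8. Expected deaths are 88 × [1 − exp(−rate × t)]: 1.1 to 4.3 by month 3 and 2.2 to 8.4 by month 6. These are the most walking tests per visit that could fall due after death.

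**The case against.** Much of the plan's choice is sound. Kaplan–Meier is right for all-cause death. Cox regression with deaths censored validly estimates the cause-specific hazard ratio for first admission, and it can be extended to recurrent events. Time to first admission is a legitimate endpoint. A composite of hospitalization or death would remove the competing-event problem, and the wording does not exclude one. A patient who dies after an admission has already had the event, so only deaths without a prior admission create the bias. The eligibility criteria select stable patients, which may keep such deaths few. Section 1 calls the analyses of functional and clinical parameters exploratory. Detail on deaths may also sit in a fuller plan that is not shown.

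All of this stands, and it confines the bias to the Kaplan–Meier probabilities of hospitalization. It does not remove the mismatch, because the article itself pairs these methods with a hospitalization rate, which neither gives in ordinary use.

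Two stronger readings are tempting. A reader might infer that the plan treats death as censoring or as ordinary missing data, so that multiple imputation would invent walking distances for patients who have died. The article states neither rule; its imputation sentence simply carries no exception for death. No bias in the 6-minute walk has been shown either, since the imputation model is not given. A reader might also take section 1 as evidence of high mortality in this cohort. It reports associations of inactivity and poor performance with mortality, and gives no level.

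**Conclusion.** The point holds for hospitalization. Used in their ordinary form, the named methods do not estimate the stated rate and leave repeat admissions uncounted; this needs no assumed figure. If deaths without a prior admission are censored, Kaplan–Meier never understates the probability of admission and generally overstates it. How far is conditional on assumed constant hazards: under 2 points at 6 months, up to 5 at 12 months and roughly 1 to 11 at 24 months. The bias need not cancel between arms.

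The imputation part is only a request for clarity and would concern a handful of patients by month 6. Scoring patients unable to walk as 0 m is a choice of estimand on which statisticians differ, and it is not part of this point. With long-term outcomes secondary, the priority is low to moderate.

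**What to change.** Revise the sentence in section 3.10 so that each quantity has its own method:

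- **All-cause death:** keep Kaplan–Meier and Cox.
- **First hospitalization:** report cumulative incidence with death as a competing event (Aalen–Johansen), and keep Cox as a cause-specific model.
- **Hospitalization rate:** model the number of admissions per patient, for example by negative binomial regression with log follow-up time as offset.

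State that multiple imputation applies only to patients alive at the visit in question, and report deaths beside the 6-minute walk results. Reconcile the 24-month horizon in section 3.6 with the 12-month close-out in Table 1, and say from which date time is counted.

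The cost is wording and slightly more programming, possibly outside the two packages named. No extra patients are needed. The count model does require that every admission and each patient's follow-up time be recorded.

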To fulfill these requirements in the ESKD population, several physical, psychological and environmental barriers that are still present need to be overcome. First, the identification of sustainable programs with good adherence is a priority because of these barriers [18,19,20]. Moreover, a proactive dialysis staff attitude is another crucial issue [21,22]; unfortunately, physical activity and exercise management are not routinely addressed in the care of these patients [2]. Although motivators to exercise have been reported in other diseases [23], nurse-led disease management programs in patients on dialysis have been tested [24,25] but not for promoting physical activity.

This pragmatic trial aims to test the impact of the regular presence of an exercise facilitator in a dialysis center to promote physical activity in the ESKD population. The efficacy will be verified in terms of applicability and feasibility, and the preferred and most effective exercise pathways for the patients will be identified. Secondarily, the study aims to carry out exploratory analyses to evaluate the impact of different exercise interventions on the functional and clinical parameters of the patients.

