### 3.8. Sample Size

To the best of our knowledge, this is the first trial of this type exploring patient preferences about programs and comparing the outcomes for these programs. Therefore, a power calculation hypothesizing a better effect of one program compared to another could not be performed; in addition, the investigators do not assign the interventions, and they do not know a priori how many patients will select each training option.

Otherwise, we aim to recruit a sufficient number of participants to address the study’s implementation objectives. The Nephrology Unit at the University Hospital of Ferrara manages approximately 140 patients on dialysis. The entrance of new patients into dialysis service will be checked every 3 months. We will try to propose the programs to all eligible patients and hypothesize a 50% rate of acceptance, which might be progressively increased by word of mouth among patients.

According to a power calculation based on a theoretical responder rate of 50% and considering a margin of error equal to 5% and a confidence level of 90%, a total of 88 patients will be required to make the first qualitative phase of the study representative of the population.

To optimize recruitment, all members of the Nephrology Unit of the hospital will be informed about the trial during team meetings. Information on the study procedures will also be given to the CKD and ESKD support groups, which will share the study information through their newsletters and website.

The EF will be available daily in the dialysis room to encourage patient participation. Informative material will also be available in the Nephrology Unit wards.

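### The planned post hoc power analysis cannot determine clinical impact; estimates in meters with confidence intervals can, and the status of the 6-min walking test needs one consistent statement

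*Protocol article*

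**What the plan says.** The last analysis that Section 3.10 lists for Phase 2, before the analysis sets and missing data, is this: "a post hoc power analysis will also be carried out to determine the clinical impact of the findings". The article does not say at which effect the power will be computed. The same section plans a two-way repeated-measures analysis of variance for the primary and secondary outcomes, with linear mixed models as a secondary analysis if baseline characteristics differ, and says that a p "value of 0.05 will be considered statistically significant".

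Section 3.8 explains why nothing was calculated in advance for the comparison of programs: "a power calculation hypothesizing a better effect of one program compared to another could not be performed", and the investigators add that "they do not know a priori how many patients will select each training option". The one sample size given, 88 patients, concerns the responder rate in Phase 1.

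On the status of the walking test, Section 3.6 says: "The primary outcome will be exercise capacity, assessed through the 6-min walking test". Table 1 also marks it as primary, in its Phase 2 block. The Introduction makes applicability and feasibility the main aim and continues: "Secondarily, the study aims to carry out exploratory analyses to evaluate the impact of different exercise interventions on the functional and clinical parameters".

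**The concern.** The plan gives a statistical quantity a task that it cannot perform. Clinical impact is a question about how many meters patients gain and whether a gain of that size matters. Power is the probability that a test rejects under some assumed effect. Computed from the observed effect, it repackages the p value.

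The sentence matters because the article states no important difference for the 6-min walking test. As written, post hoc power is the only tool named for judging clinical impact. Section 4.2 itself expects selection bias and a possibly small sample, so an imprecise comparison is a realistic outcome. A power figure could then be read as evidence about clinical value that it does not contain.

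A smaller, related point is that the article does not say plainly whether a walking-test result at the 0.05 level is to be read as a primary finding or an exploratory one.

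**Working it through.** The plan gives no power figure to reproduce. The check is whether post hoc power can carry information about meters walked.

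**Inputs.** Significance level 0.05 (Section 3.10; sidedness is not stated, so two-sided is assumed). Four options (Section 3.2). Three visits: baseline, 3 months and 6 months (Section 3.6). 88 patients (Section 3.8), used here only as an assumed number analyzed. Power is taken at the observed effect, which is also an assumption.

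**1. One degree of freedom.** With z the observed absolute test statistic, observed power = Φ(z − 1.96) + Φ(−z − 1.96). The only input is z, and z is fixed by p.

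| p | z | Observed power |
|---|---|---|
| 0.01 | 2.576 | 73% |
| 0.05 | 1.960 | 50% |
| 0.20 | 1.282 | 25% |
| 0.50 | 0.674 | 10% |

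**2. The planned analysis of variance.** With 88 patients, four groups and three visits, the group-by-time test has (4 − 1)(3 − 1) = 6 and (88 − 4)(3 − 1) = 168 degrees of freedom. Take the noncentrality as 6 × F, where F is the observed statistic. Power is then the probability that a noncentral F exceeds the 5% critical value of 2.153.

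| p | F | Noncentrality | Observed power |
|---|---|---|---|
| 0.05 | 2.153 | 12.92 | 76% |
| 0.20 | 1.446 | 8.67 | 55% |
| 0.50 | 0.895 | 5.37 | 35% |

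The percentages are higher than for the z test, but each is again determined by p alone.

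**3. Different effects, same power.** Three invented pairwise results, with z = difference / (SD × √(2/n)). The SDs and arm sizes are illustrative and are not in the article; 22 per arm is 88/4.

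| Difference | SD | n per arm | Standard error | z | p | Observed power | 95% confidence interval |
|---|---|---|---|---|---|---|---|
| 50 m | 100 m | 22 | 30.15 m | 1.658 | 0.097 | 38% | −9 to 109 m |
| 10 m | 20 m | 22 | 6.03 m | 1.658 | 0.097 | 38% | −2 to 22 m |
| 10 m | 100 m | 550 | 6.03 m | 1.658 | 0.097 | 38% | −2 to 22 m |

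Observed power does not separate the first row from the other two. The estimate and its interval (difference ± 1.96 × standard error) do: the first row is compatible with a difference of 100 m, while the others rule out anything much above 20 m.

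**4. Status of the walking test.** Section 3.6 and Table 1 call it primary, both under a Phase 2 heading. The Introduction calls the analyses of functional and clinical parameters secondary and exploratory without naming the test. A 6-min walk is plainly a functional measure. The two can be reconciled if primary means leading within Phase 2, but no sentence says so.

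**The case against.** The strongest reply is that Section 3.10 does not say the power will be taken at the observed effect. Power at a stated relevant difference, using the arm sizes actually achieved, is not a function of p, and those sizes could not be known beforehand. This stands as a limit on the argument from the p value. It does not save the sentence: such a calculation shows what the trial could have detected, not the clinical impact of what was found, and the article states no relevant difference for it.

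A reader might infer that post hoc power stands in for a missing power calculation. The article does not say that. Section 3.8 gives its reasons openly, the lack of a comparative calculation is acceptable in a feasibility trial, and Section 3.10 presents the post hoc analysis as an addition.

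A reader might also infer that every non-significant result will show low post hoc power. That is too strong. Under the assumed 6 and 168 degrees of freedom, p = 0.20 gives 55%. The one-degree-of-freedom percentages illustrate the principle and do not describe the planned analysis of variance.

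Finally, the primary and exploratory labels can be read together, as shown above. This weakens that part to a matter of clarity.

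**Conclusion.** The concern holds in a limited form. The stated purpose of the post hoc power analysis is wrong as written, because no kind of power measures clinical impact. If power is taken at the observed effect, the figure adds nothing to the p value: 50% at p = 0.05 for a one-degree-of-freedom z test, and about 76% at p = 0.05 for a group-by-time F test under the assumption of 88 patients, four groups and three visits. The exact percentages depend on those assumptions; the conclusion does not.

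The inconsistency over the walking test is real but mild. It does not follow that the Phase 1 responder rate must become the trial's primary outcome, or that significance tests on walking distance must be barred. Either would be a preference, not a correction that the text requires.

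**What to change.** Delete the post hoc power analysis from Section 3.10. In its place, state that clinical impact will be judged from the adjusted between-program and within-program changes in 6-min walking distance, in meters with 95% confidence intervals, against a minimal important difference that the investigators fix and justify before the data are analyzed. The mixed models already foreseen in Section 3.10 can supply the adjusted estimates.

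Make the status of the walking test the same in the Introduction, Section 3.6 and Table 1. One workable wording is that it is the lead outcome of Phase 2 and that its between-program comparisons are exploratory.

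The cost is a few sentences and the choice of one threshold. No patients, visits or data are added. The only loss is one conventional figure that is no longer reported.
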